### Sample size

The primary outcome of the study is mean length for age Z (LAZ) score at 18 months. In a meta-analysis of complementary feeding trials testing interventions to improve growth, nutrition education interventions had a mean effect size of 0.2 Z scores on LAZ at 18 months (range 0.04, 0.64) [38]. We therefore chose 0.15 as a conservative estimate of the effect size. The intra-cluster correlation (ICC) for stunting was estimated at 0.035 using an analysis of 42 DHS studies and our own data from the study areas [43]. The unit of randomisation (cluster) is a village and its attached hamlets. We expect around 25 live births per year in each cluster. Accounting for 10% attrition due to loss to follow-up and mortality, recruiting all eligible children born over 12 months in 110 clusters (2772 children before and 2520 after attrition), will allow us to detect a difference of 0.15 in mean LAZ scores between intervention and control arms (SD of 1) with 80% power and alpha of 0.05, and a design effect (D) of 1.8, calculated as D = 1 + (25–1) x 0.035. This sample size also gives the trial 80% power to detect a 13% reduction in the prevalence of stunting (from 60% to 52.5%), a 19% reduction in the prevalence of wasting (from 40% to 32.5%), and a reduction in the infant mortality rate greater than 45% (from 100 to 55 per 1000 livebirths) [44]. To account for the possibility of clusters dropping out of the study and for attrition rates exceeding our 10% estimate, we enrolled a total of 120 clusters (villages).

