### Data collection, cleaning and storage

Across the study area, incentivised volunteers report pregnancies to monitors, each responsible for a population of around 4000. A monitor visits every pregnant woman identified, ascertains the estimated month of pregnancy, offers information about the study and invites her to join. If consent is given, the monitor measure the woman’s height and MUAC, and administers a first questionnaire. All children born to pregnant women recruited between 1st October 2013 and 10th February 2015 will be followed up within 72 hours of birth, and at 3, 6, 9, 12 and 18 months. Trained growth monitors conduct measurements at birth, and then visit the mother and child at 3, 6, 9, 12 and 18 months to measure length (using a Shorr board), weight (using a Seca 384 scale), MUAC, and administer a structured questionnaire. All monitors’ measurements were validated twice against a gold standard, and we calculated intra-observer and inter-observer technical error of measurement for length and other anthropometric outcomes.

We use mobile phones programmed using the CommCare platform for data collection. The monitoring team checks the number of interviews completed and type of data collected every week in order to promptly identify and address possible problems. The data are downloaded every two weeks and checked for errors using automated do files and manual inspections. Names of participants are collected but removed before data storage. Final datasets contain numerical identifiers for cluster individual participants. The data are stored and backed up every two weeks on a server.

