#### Final analysis

Final analyses will be by intention-to-treat and include all mothers who were pregnant and had a live birth during the recruitment period (1st October 2013 – 10th February 2015) and their infants, regardless of whether they received the intervention or not. We will test for differences between intervention and control areas in the main outcomes of interest using linear regression for continuous outcomes and logistic regression for binary outcomes, adjusting for clustering using random effect models. We will examine levels of missing data for the primary and secondary outcomes, and plan to use multiple imputation if these exceed 10%.

For the final DMC, we plan to carry out three sub-group analyses. The first will examine differences in children’s LAZ at 18 months according to the intensity of their mothers’ exposure to group meetings (number of meetings attended), adjusting for maternal education, multi-dimensional poverty status, and tribal status. The second sub-group analysis will examine differences in growth outcomes between arms by wealth quintile to understand the equity impact of the intervention. The third sub-group analysis will examine differences in growth outcomes for boys and girls. The final analysis will be presented according to the CONSORT requirements for cluster randomised controlled trials [46,47]. Both the interim and final analyses will be conducted by the trial statistician ([name]).

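### Imputation starts only above 10% missing, about the attrition the plan expects, so the 18-month LAZ analysis would leave unused the earlier lengths of living children; the likely bias is modest

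*Protocol article*

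**What the plan says.** The Final analysis section of the protocol article compares the arms by linear regression for continuous outcomes, with random effects for clustering. It describes no repeated-measures model. Its one rule for missing data is: "We will examine levels of missing data for the primary and secondary outcomes, and plan to use multiple imputation if these exceed 10" per cent. It does not say whether that level is taken overall or by arm, or whether deaths and excluded children count towards it. On the population it says: "Final analyses will be by intention-to-treat and include all mothers who were pregnant and had a live birth during the recruitment period", together with their infants.

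Three other sections bear on the rule:

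- **Sample size.** The calculation is described as "Accounting for 10% attrition due to loss to follow-up and mortality". The counts are "2772 children before and 2520 after attrition", and the target is a LAZ difference of 0.15 with an SD of 1.
- **Data collection, cleaning and storage.** Growth monitors measure children at birth and "then visit the mother and child at 3, 6, 9, 12 and 18 months to measure length".
- **Trial participants.** Neonatal deaths are excluded, among other groups. So are mother/infant pairs who miss more than two interviews in a row, who are treated as permanent migrants.

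**The concern.** The threshold for imputation sits at the attrition the plan already expects. When missingness is at or below it, the only stated analysis uses children with a measured 18-month length. A living child seen at 9 or 12 months but not at 18 then contributes nothing to the primary comparison, although the earlier LAZ is informative about the missing value.

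The level of missing data is also the wrong quantity to act on. Bias in the arm contrast arises when missingness differs between arms, or relates differently to growth in the two arms. A low percentage rules out neither. Differential loss is plausible here, because only intervention families receive monthly worker visits and participants are not blinded. If poorly growing control children are lost more often, the contrast is pulled towards no effect; the reverse pattern inflates it. With a target of only 0.15 Z and planned power of about 80%, even a modest shift deserves to be avoided when the data to reduce it are already collected.

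**Working it through.** **1. The plan's sample size.** Children per arm before clustering: 2 × (1.960 + 0.842)² × 1² / 0.15² = 698. With two arms and the stated design effect of 1.8: 2 × 698 × 1.8 = 2513, against 2520 in the article. The figure is reproduced.

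**2. Does the planned attrition reach the trigger?** 2772 − 2520 = 252, and 252 / 2772 = 9.1%. Exceeding 10% of 2772 needs more than 277 children. Had the inflation been done by division, 2520 / 0.9 = 2800, and 280 / 2800 is exactly 10.0%, which still does not exceed 10%.

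**3. How many of the 252 are living children?** The article does not say. Assuming 3% or 5% of the 2772 die within that attrition:

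- 3%: 83 deaths, leaving 252 − 83 = 169 living (6.1% of 2772).
- 5%: 139 deaths, leaving 252 − 139 = 113 living (4.1% of 2772).

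The group at issue is therefore about 4 to 6%, before any migration exclusion. I use 5%.

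**4. What earlier data do they have?** Missing the 9-, 12- and 18-month interviews would be three in a row and lead to exclusion. On that count, a retained child without an 18-month visit had an interview at 9 or 12 months, normally with a length.

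**5. Bias of the analysis of observed lengths.** In each arm, the observed mean exceeds the full mean by p × g, where p is the proportion missing and g is the gap in mean LAZ between observed and missing children. With the same g in both arms, the bias in the contrast (intervention minus control) is (p_I − p_C) × g. The splits and gaps are assumptions; the article gives none.

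| Missing, intervention v control | g = 0.3 | g = 0.7 | Share of 0.15 |
|---|---|---|---|
| 3.5% v 6.5% (5% overall) | −0.009 | −0.021 | 6 to 14% |
| 7% v 13% (10% overall, all living) | −0.018 | −0.042 | 12 to 28% |
| equal in both arms | 0 | 0 | 0 |

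Reversing the split reverses the sign. In the first row neither arm passes 10%, so imputation is not triggered whether the level is read overall or by arm. The second row escapes the trigger only if the level is read overall.

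**6. Equal loss with a different gap.** The bias is then p × (g_I − g_C). At 5% missing in each arm and a gap that differs by 0.25 or 0.5 Z, it is 0.0125 or 0.025 Z (8% or 17% of 0.15). Equal percentages alone are not a safeguard.

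**7. Against sampling error.** The planned standard error is √(2 × 1.8 / 1260) = 0.053. The first row is therefore about 0.2 to 0.4 standard errors.

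**The case against.** The strongest objection is about size. A reader might infer that 10% of children are alive and dropped, which would put the bias at 12 to 28% of the target. The documents do not support that. The 10% includes mortality, the same section works with infant mortality of 100 per 1000 live births, and neonatal deaths and permanent migrants are excluded. This stands, and it roughly halves the figures.

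Second, whether imputation is triggered depends on an unstated denominator. If deaths count as missing, mortality of 100 per 1000 plus any loss would pass 10%. If they do not, missingness among living, eligible children is probably well below 10%. This also stands, but it does not rescue the rule: in the first case lengths might be imputed for children who have died, and in the second the earlier lengths go unused. That the default is an analysis of observed lengths is itself an inference, since the article does not name it; nothing else is stated for that situation.

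Third, a reader might infer that the method is chosen after looking at outcomes. It is not. The rule looks at levels of missing data, the threshold is fixed in advance, and the Blinding section has the statistician working blind to allocation.

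Fourth, imputation details and sensitivity analyses commonly sit in a statistical analysis plan. That is true, but the trigger is stated in the article, so it can be judged as it stands.

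**Conclusion.** The point holds in a limited form. On the plan's own counts, the expected attrition (9.1%, or 10.0% at most) does not trigger imputation. The stated analysis of 18-month LAZ then rests on observed 18-month lengths and leaves unused the 3- to 12-month LAZ of living, eligible children without one. The percentage missing is a poor basis for that decision.

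The likely bias is modest: about 0.009 to 0.021 Z (6 to 14% of 0.15), if 5% of living, eligible children are missing, split 3.5% v 6.5%, and lost children average 0.3 to 0.7 Z lower. It reaches 0.018 to 0.042 Z only if the full 10% are living children split 7% v 13%. It is about zero if loss is equal and depends on LAZ in the same way in both arms. The article supports none of these splits or gaps over the others, so no particular bias can be said to be expected. The case for change is that a better rule costs little.

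**What to change.** Drop the 10% trigger. Pre-specify that the primary analysis uses earlier LAZ whatever the percentage missing, in one of two ways:

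- multilevel multiple imputation of 18-month LAZ, done by arm and with cluster effects, restricted to children alive at 18 months and not excluded under Trial participants; or
- an equivalent longitudinal mixed model of LAZ in that same set, with the arm contrast read at 18 months.

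The restriction matters. Admitting every child with at least one length after birth would bring in children who later die and permanent migrants, and the model would implicitly extrapolate their growth to 18 months. State how deaths are handled, separately from missing lengths. Report the analysis of observed 18-month lengths as a sensitivity analysis, with missingness by arm.

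The cost is wording and slightly more analysis work, with no new data, visits or children. The article describes the trial as still recruiting, so the change can be pre-specified. The downside is an assumption that data are missing at random given earlier LAZ. Some bias can remain where the 12-month value is also missing, or where loss depends on growth that was never observed.

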### Process evaluation

A process evaluation will document the design, implementation and mechanisms of the intervention to enable replication and scale up. Five main sources of data will be used: (a) project planning and monitoring documents; (b) forms to capture attendance, problems and strategies identified by the women’s groups; (c) SPK home visit diaries noting the three main issues discussed during visits; (d) around 20 semi-structured interviews (data will be collected until saturation) with mothers of children under-2 in the experimental arm and eight focus group discussions with small family groups, SPKs, *Anganwadi*s and ASHAs to document perceptions of the intervention and its effects; (e) field notes from intervention team members to be reviewed through monthly debriefings will document intervention events.

### Economic evaluation

We will conduct cost and cost-effectiveness analyses to guide policy decisions and inform any subsequent scale up. We will estimate the total and incremental costs of the intervention from a project, provider, household and societal perspective. The project costs of delivering the interventions will be collected prospectively from the project accounts using a standardised data capture tool designed for this purpose in Excel, and converted to economic costs. Costs incurred by health care providers (mainly MTCs in the districts) will be collected using trial monitoring data on the change in service use, combined with key informant interviews and available financial data on the average unit cost of delivering those services. Patient (household) costs will be collected prospectively during follow-up surveys. All costs will be adjusted for inflation using the Indian Consumer Price Index (CPI) and will be presented in Indian Rupees and 2016 International Dollars. Incremental cost-effectiveness will be measured in relation to the *status quo* alternative i.e. doing nothing in addition to the current ongoing activities. Incremental cost-effectiveness ratios (ICERs) will be calculated for the primary outcome measure (i.e. cases of stunting prevented) and selected secondary and summary measures including cases of wasting prevented, cases of infant mortality averted, life-years saved and DALYs averted. Sensitivity analyses will be carried out to assess the robustness of results.

### Ethical issues

The study received ethical approval from the research ethics committee of the Public Health Foundation of India (June 2013, TRC-IEC-163/13), an Independent Ethics Committee linked to Ekjut (May 2013), and University College London’s Research Ethics Committee (June 2013, reference 1881/002). We identified and sought to address five main ethical concerns.

#### 1. The need for cluster-level and individual-level informed consent for participation in the trial

We sought cluster-level consent from village leaders and village health, sanitation and nutrition committee members after explaining the study aims, intervention and data collection procedures. We also seek individual consent from mothers prior to each interview and measurement session; consent is in writing or by thumbprint at the first interview, and verbally for subsequent interviews.

#### 2. Identification of severely acutely malnourished children

For ethical reasons, severely acutely malnourished (SAM) children identified by the study monitoring team in both intervention and control arms are all referred to the *Anganwadi Sevika* for onward referral to the local MTC.

#### 3. Benefits to control areas

In addition to the referral of SAM children in both arms, we are implementing a capacity building intervention for local VHSNCs in both the trial intervention and control arms.

#### 4. Impact of the intervention on existing health services

The trial activities can have several repercussions, both positive and negative, on NRHM and ICDS services. First, we expect our work with VHSNCs to impact on the provision and uptake of local health and nutrition services, including demand for, and utilisation of, Malnutrition Treatment Centres. We will monitor process indicators for the VHSNC intervention by assessing members’ awareness of entitlements and service guarantees at the beginning and end of the intervention through a questionnaire. We will also measure changes in the utilization of MTCs. Secondly, it is possible that the presence of a second health and nutrition worker may cause tension with other community workers. It is therefore critical for the study team and SPKs to establish role and supervision boundaries with the districts’ ICDS and NRHM teams prior to the start of the study, and for the SPKs to establish a rapport with existing community health workers at the beginning of the intervention. This was done by engaging these workers in the selection of the SPKs and with an introductory meeting between SPKs and other workers at the outset.

#### 5. Use of a parallel trial design

Finally, the use of a parallel design for this study has ethical limitations: in areas with such high levels of stunting and where no group meetings or home visits are available to mothers and children, the equipoise of this study (i.e. genuine uncertainty over its benefits) can be questioned. However, we selected this design over a stepped-wedge approach due to concerns about the increased sample size that a stepped-wedge design might entail and the lengthy time frame required to implement a sufficient number of steps. We believe that operational research studies such as this would benefit from further methodological work on alternative approaches to parallel-design trials, including phased designs [48].

### Intervention sustainability and scalability

We developed the community strategy to be manageable for a single community-based worker within existing NRHM and ICDS systems. *Suposhan Karyakartas* have similar educational levels as *Anganwadi Sevikas*, the same stipend and the same supervisor to worker ratio (1:10). The trial results will be generalisable to rural areas of India with a high proportion of poor, Scheduled Tribe and Scheduled Caste communities. We estimate that these constitute at least 70% of ICDS’ 200 high-burden districts across India, or a population of over 170 million. We will seek to maximise generalisability and impact through three strategies. First, engagement with the health system will start from the village-level, as the SPK will aim to work in collaboration with existing frontline workers and the VHSNCs. Second, we will engage with ICDS and NRHM implementers at the onset, midpoint and end of the study to ensure the intervention’s compatibility with existing systems and maximise its scalability. Third, if the strategy improves the trial’s primary and/or secondary outcomes, we will use our cost-effectiveness estimates and process evaluation data, together with socio-demographic and health systems data from the 200 ICDS high-burden districts, to assess the scalability of the intervention through NRHM and ICDS systems, and to model the potential costs and impact of the intervention scaled up to all or parts of the high-burden districts.

### Trial timeline and status

The trial is planned for a duration of 46 months (1st April 2013 – 31st January 2017) and is currently recruiting participants.

## Abbreviations

ANM: Auxiliary Nurse Midwife
ASHA: Accredited Social Health Activist
AWW: Anganwadi Worker
DMC: Data monitoring committee
ICDS: Integrated Child Development Services
NGO: Non-government organization
NRHM: National Rural Health Mission
SD: Standard deviation
SPK: *Suposhan Karyakarta*
